# LIST OF ABBREVIATIONS

The following abbreviations and special terms are used in this clinical study Protocol.

| **Abbreviation** | **Definition** |
| --- | --- |
| AE | adverse event |
| acute GVHD | acute graft-versus-host disease |
| allo-HSCT | allogeneic hematopoietic stem cell transplantation |
| ALP | alkaline phosphatase |
| ALT | alanine aminotransferase |
| ANC | absolute neutrophil count |
| AST | aspartate aminotransferase |
| BMT | Bone Marrow Transplant |
| CI | confidence interval |
| CFR | Code of Federal Regulations |
| cGVHD | chronic graft-versus-host disease |
| CIBMTR | Center for International Blood and Marrow Transplant Research |
| CMV | cytomegalovirus |
| CR | complete response |
| CSA | cyclosporine A |
| CTCAE | Common Terminology Criteria for Adverse Events |
| DFS | disease-free survival |
| DLT | dose-limiting toxicity |
| DMC | Data Monitoring Committee |
| DNA | deoxyribonucleic acid |
| DOR | duration of response |
| EBV | Epstein–Barr virus |
| ECOG | Eastern Cooperative Oncology Group |
| eCRF | electronic case report form |
| EOT | end of treatment |
| **Abbreviation** | **Definition** |
| FDA | Food and Drug Administration |
| FFS | failure-free survival |
| GCP | Good Clinical Practice |
| GI | gastrointestinal |
| GVH | graft versus host |
| GVHD | graft-versus-host disease |
| GVT | graft versus tumor |
| HBsAg | hepatitis B surface antigen |
| HBV | hepatitis B virus |
| HCV | hepatitis C virus |
| HLA | human leukocyte antigen |
| HSCT | hematopoietic stem cell transplant |
| ICF | informed consent form |
| IFN-γ | interferon-γ |
| IFN-γR | interferon-γ receptor |
| IL | interleukin |
| IL-2R | interleukin 2 receptor |
| IQR | interquartile range |
| JAK | Janus kinase |
| LLN | lower limit of normal |
| MAGIC | Mount Sinai Acute GVHD International Consortium |
| MAP | MAGIC algorithm probability |
| NIH | National Institutes of Health |
| NK | natural killer |
| NRM | nonrelapse mortality |
| ORR | overall response rate |
| OS | overall survival |
| PCR | polymerase chain reaction |
| **Abbreviation** | **Definition** |
| PO | orally |
| PR | partial response |
| PTLD | post-transplant lymphoproliferative disorder |
| QD | once daily |
| REG3α | regenerating islet-derived 3-alpha |
| RNA | ribonucleic acid |
| SAE | serious adverse event |
| SR | steroid-refractory |
| sST2 | soluble suppression of tumorigenesis-2 |
| STAT | signal transducers and activators of transcription |
| sSTNFR1 | soluble tumor necrosis factor receptor 1 |
| TNF | tumor necrosis factor |
| Treg | regulatory T cell |
| TTR | time to response |
| TYK | tyrosine kinase |

# 1. INTRODUCTION

## 1.1. Overview of Acute Graft-Versus-Host Disease

Acute graft-versus-host disease (acute GVHD) remains a major transplantation-related complication despite standard prophylaxis ^[1-31]^. Systemic corticosteroid therapy is the first-line treatment for newly diagnosed acute GVHD patients ^[4, 5]^. However, steroid-refractory acute GVHD (SR-acute GVHD) occurs in approximately 35–50% of patients and is associated with high mortality ^[1, 6-8]^, indicating an intrinsic variability of glucocorticoid sensitivity at acute GVHD onset ^[9]^. The steroid resistance in recurrent acute GVHD further supports this speculation ^[4]^. Enhancing glucocorticoid sensitivity in newly diagnosed acute GVHD patients for the first-line therapy could result in therapeutic benefit. Methylpredinisone at a dose of 2 mg/kg also renders patients susceptible to infections, osteoporosis, and various metabolic disturbances ^[8, 10]^. Thus, there is an urgent requirement for novel active first-line treatments to improve efficiency and decrease the side effects in newly diagnosed acute GVHD patients.

The pathogenesis of acute GVHD is complicated. Early tissue injuries, the activation of innate immune cells and donor T cells, and the subsequent immune response lead to healthy tissue damage ^[11, 12]^. Janus kinases (JAKs) are intracellular signaling molecules that regulate the activities of immune cells, including neutrophil cells, antigen-presenting cells, T cells, and B cells underlying GVHD, and therefore regulate acute GVHD pathogenesis ^[11, 13]^. Cytokines and chemokines such as interleukin (IL) -1, interferon-gamma, IL-2, tumor necrosis factor, IL-6, IL-17, and IL-33 are involved in GVHD pathogenesis ^[5, 11, 14]^. Intracellular signaling downstream of multiple cytokines related to acute GVHD is partialy transduced by JAK signaling pathways ^[15]^.

## 1.2. MAGIC Algorithm Probability

The clinical stage of acute GVHD is defined according to each involved organ’s clinical assessment of symptoms. The organ stages are totaled in an overall grade (I–IV) ^[16]^. Grade III/IV acute GVHD is associated with high mortality rate (50%–70%) and the possibility of steroid resistance. Serum biomarkers have also emerged as an additional potential measurement of acute GVHD severity ^[17, 18]^. The Mount Sinai Acute GVHD International Consortium (MAGIC) is a group of 25 stem cell transplantation centers conducting GVHD research. It has established an algorithm that combines two biomarkers, namely ST2 and REG3α. The MAGIC algorithm probability (MAP) predicts the response to first-line treatment of corticosteroids and 6-month non-relapse mortality (NRM). When measured at acute GVHD onset, the MAP could categorize the patients into three risk groups, each group with significantly different risk of NRM. The proportion of patients resistant to treatment at week 4 was higher in the high MAP risk group than in the low-risk group (67% vs. 30%, p = 0.03) ^[14, 19]^. Therefore, novel and active first-line therapies are urgently required in patients with high-risk acute GVHD prone to steroid resistance ^[9, 20]^.

## 1.3. Ruxolitinib Background and Study Rationale

Ruxolitinib, a selective inhibitor of Janus kinase (JAK) 1/2, is the first Food and Drug Administration-approved medication for SR-acute GVHD ^[4, 15, 21]^. The REACH2 phase 3 randomized trial showed that in patients with SR-acute GVHD, the overall complete response (CR) at day 28 was higher in the ruxolitinib group than the control group (62% vs. 39%; p < 0.001). The durable overall response rate (ORR) at day 56 was significantly higher in the ruxolitinib group than that in the control group (40% vs 22%; p < 0.001) ^[22]^. The incidence of infection was similar in ruxolitinib and control therapy, with grade 3 severity of 22% and 19%, respectively. The incidence of cytomegalovirus (CMV) reactivation was 26%, and Epstein-Barr virus (EBV) reactivation was 6% in the ruxolitinib group ^[22]^. Delgado MC et al. showed that ruxolitinib enhances cell sensitivity to dexamethasone-induced apoptosis in vitro. The combination of corticosteroid and ruxolitinib alteres the balance between pro- and anti-apoptotic factors in cells with corticosteroid resistance ^[23]^. Thus, the addition of ruxolitinib may improve the efficacy of corticosteroids in SR-acute GVHD patients. Treatment with methylprednisolone at 2 mg/kg/day or prednisone at 2.0 to 2.5 mg/kg/day is the standard first-line systemic therapy for acute GVHD. Methylprednisolone is the most commonly used corticosteroid. Also, other types of steroids are available if administered at an equivalent steroid dose. In the present study, methylprednisolone was adopted to standardize the research.

We previously reported the results of the first-line treatment for newly diagnosed acute GVHD patients with a combination of different doses of ruxolitinib with corticosteroid ^[4, 24]^. This phase I dose-finding study investigated the optimal dose of ruxolitinib combined with corticosteroid (ClinicalTrials.gov Identifier: NCT04397367). The average accumulated dose of methylprednisolone was 17.6 mg/kg (standard deviation [SD] = 8.2) with a mean withdrawal time of 42.6 ± 16.8SD days. Patients were treated with three different doses of ruxolitinib: 10 mg twice daily for the first three patients, 5 mg twice daily for the following 12 patients, and 5 mg once daily for the remaining 17 patients. In the first three patients, intolerable hematologic toxicity related to 10 mg twice daily ruxolitinib was observed. CMV and EBV diseases were seen in 2 of 12 patients who received a dose of ruxolitinib 5 mg twice daily, with one suffering from CMV infection and another developing post-transplant lymphoproliferative disorder. As observed in the last 17 patients, 5 mg/day Ruxolitinib combined with methylprednisolone (1 mg/kg/day) was well tolerated with decreased CMV reactivation and promising signals of efficacy as demonstrated by 28-days ORR of 82.05% ^[24]^. After initiation of the novel first-line therapy, remission of acute GVHD in all patients occurred at a median time of 3.2 (interquartile range [IQR], 1–7) days. Of all patients, 10 patients (31.2%) developed recurrent acute GVHD after complete remission. The causes of recurrent GVHD included ruxolitinib and cyclosporine reduction (n=8) and therapeutic donor lymphocyte infusion (DLI; n=1). The relapse rate of primary disease in all patients with acute GVHD was 15.6% (5/32). With a median follow-up of 260 days, the 1-year overall survival (OS) and disease-free survival (DFS) were 73.4% (CI: 56.6%–95.1%) and 61.2% (95% CI 37.4%–95.6%), respectively. Cyclosporine A (CSA) is tapered over 60 days in the Ruxolitinib group with durable complete response. Short duration of CSA may accelerate immune reconstitution, which is good for reducing relapse of primary disease and infection. These data suggested that a regimen of ruxolitinib plus corticosteroids may improve the long-term outcomes of patients with newly diagnosed acute GVHD with tolerance.

## 1.4. Potential Risks and Benefits of the Treatment Regimen

Adverse events that have been most frequently reported in at least 10% of subjects receiving ruxolitinib monotherapy include anemia, thrombocytopenia, diarrhea, nausea, fatigue, and upper respiratory tract infection.

As a result of ruxolitinib-mediated immunomodulation, an increased incidence of infections could possibly occur with ruxolitinib therapy. Strict clinical monitoring is indicated to identify and treat infections in study subjects should they occur.

Because of the potential for myelosuppression, subjects will have hematologic parameters closely monitored during clinical studies. If there are clinically relevant declines in hematology parameters, therapy may be interrupted until resolution or discontinuation. As ruxolitinib also has the potential to cause WBC margination (ie, a transient decrease in ANC), assessment of hematology parameters should be performed before study drug administration and at all applicable study visits.

As described in 1.3., ruxolitinib in previous clinical studies shows the capability of GVHD reduction, preservation of the beneficial GVT effect, and improvement in survival.

# 2. STUDY OBJECTIVES AND ENDPOINTS

| Primary Objective | Primary Endpoint |
| --- | --- |
| Compare the efficacy of ruxolitinib in combination with 1mg/kg methylprednisolone versus 2 mg/kg methylprednisolone alone in terms of overall response rate (ORR) at Day 28 in subjects with acute graft-versus-host disease (acute GVHD). | ORR at Day28, defined as the proportion of participants demonstrating a complete response (CR), or partial response (PR) |
| Secondary Objective | Secondary Endpoints |
| Compare additional response and longer-term efficacy outcomes between treatment cohorts. | Durable ORR at Day56, defined as the proportion of patients in each arm whose response on day 28 lasts until day 56 after randomization. |
|  | DOR at Month 6 for responders will be calculated. The DOR is defined from the time of the onset of response to loss of response. Subjects who died or discontinued will be censored at the  death date or the previous assessment. |
|  | Response duration, defined as the time from the first response to the first recurrence/progression of acute GVHD or additional immunosuppressants for GVHD. |
|  | NRM at Month 24, defined as the time from enrollment to death due to any causes other than hematologic disease relapse. |
|  | Cumulative incidence of relapse (CIR) at Month 24, defined as the proportion of subjects whose underlying hematologic disease relapses. |
|  | Disease-free survival (DFS) at Month 24, defined as the time from enrollment to relapse of primary disease or death from any causes, whichever occurred first. |
|  | Failure-free survival (FFS) at Month 24, defined as the time from randomization to disease relapse or progression, non-relapse mortality, or the addition of new therapy for acute GVHD. |
|  | Overall survival (OS) at Month 24, defined as the time from randomization to death due to any causes. |
| Assess the incidence and severity of adverse events (AEs) and serious adverse events. | Clinical safety data (eg, AEs, infections) will be tabulated and listed. |
| Evaluate the use and discontinuation of  corticosteroids. | Average and cumulative corticosteroid dose at Days 365; proportion of subjects who discontinue corticosteroids at Days 56 and 100. |
| Evaluate the use and discontinuation of  immunosuppressive medications. | Proportion of subjects who discontinue immunosuppressive medications at Days 365. |
| Evaluate the incidence of recurrent acute GVHD. | Incidence rate of recurrent acute GVHD through Month 12. |
| Evaluate the incidence of cGVHD. | Incidence rate of cGVHD at Month 24. |

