| \| **Primary Objective** \| **Primary Endpoint** \| \| --- \| --- \| \| Compare the efficacy of ruxolitinib in combination with corticosteroids versus corticosteroids in terms of overall response rate (ORR) at Day 28 in subjects with acute graft-versus-host disease (acute GVHD). \| ORR at Day28, defined as the proportion of participants demonstrating a complete response (CR), or partial response (PR) \| \| **Secondary Objective** \| **Secondary Endpoints** \| \| Compare additional response and longer-term efficacy outcomes between treatment cohorts. \| Durable ORR at Day56, defined as the proportion of patients in each arm whose response on day 28 lasts until day 56 after randomization. \| \| DOR at Month 6 for responders will be calculated. The DOR is defined from the time of the onset of response to loss of response. Subjects who died or discontinued will be censored at the  death date or the previous assessment. \| \| Response duration, defined as the time from the first response to the first recurrence/progression of acute GVHD or additional immunosuppressants for GVHD. \| \| NRM at Month 24, defined as the time from enrollment to death due to any causes other than hematologic disease relapse. \| \| Cumulative incidence of relapse (CIR) at Month 24, defined as the proportion of subjects whose underlying hematologic disease relapses. \| \| Disease-free survival (DFS) at Month 24, defined as the time from enrollment to relapse of primary disease or death from any causes, whichever occurred first. \| \| Failure-free survival (FFS) at Month 24, defined as the time from randomization to disease relapse or progression, non-relapse mortality, or the addition of new therapy for acute GVHD. \| \| Overall survival (OS) at Month 24, defined as the time from randomization to death due to any causes. \| \| Assess the incidence and severity of adverse events (AEs) and serious adverse events. \| Clinical safety data (eg, AEs, infections) will be tabulated and listed. \| \| Evaluate the use and discontinuation of  corticosteroids. \| Average and cumulative corticosteroid dose at Days 365; \| \| Evaluate the use and discontinuation of  immunosuppressive medications. \| Proportion of subjects who discontinue immunosuppressive medications at Days365. \| \| Evaluate the incidence of recurrent acute GVHD \| Incidence rate of recurrent acute GVHD through Month 24. \| \| Evaluate the incidence of cGVHD. \| Incidence rate of cGVHD at Month 24. \| \| **Overall Study Design:**  This trial is an open-label, multicenter, prospective randomized two-arm phase II study comparing the efficacy and safety of ruxolitinib plus methylprednisolone (1 mg/kg) vs. methylprednisolone (2 mg/kg) alone. The biomarkers of acute GVHD, such as sST2, sTNFR1, IL-6, IL-8, and REG3α will be tested at acute GVHD onset. Patients with newly diagnosed intermediate-risk or high-risk acute GVHD, as defined by Minnesota acute GVHD risk score and the biomarker score will be included. The treatment efficacy will be evaluated with respect to the level of biomarkers and clinical manifestations. Written informed consent must be obtained from the patients before enrollment in the study. The consent form and related materials are available from the corresponding author on request.  **Study Population:**  Eligible patients with intermediate-risk or high-risk acute GVHD graded according to the modified Glucksberg criteria, Minnesota acute GVHD risk score and the biomarker score and untreated with systemic acute GVHD therapy will be enrolled in this study.  **Key Inclusion Criteria:**   - Male or female, 14 to 65 years old. - Have undergone first allogeneic hematopoietic stem cell transplantation (allo-HSCT) from any donor source using bone marrow, peripheral blood stem cells, or cord blood for hematologic malignancies. - Develop a de novo acute GVHD, defined as intermediate- or high-risk using the Minnesota acute GVHD risk score and MAGIC biomarker algorithm.   **Key Exclusion Criteria:**   - Has received more than one allogeneic stem cell transplant. - Female patients with pregnant or breast-feeding. - Has Acquired Immune Deficiency Syndrome (AIDS), or hepatitis B/C infection, uncontrolled bacterial, fungal, or viral infections. - Allergies to ruxolitinib. - Vital organ dysfunction unrelated to GVHD, including persistent bilirubin abnormalities or severe heart and respiratory diseases. - Relapse of the primary disease or graft rejection after transplantation. - Presence of GVHD overlap syndrome. - Presence of cGVHD or associated clinical signs or DLI-induced acute GVHD or interferon. - Previous history of JAK1/2 inhibitor treatment after transplantation, except JAK inhibitors administered before the transplantation. - absolute neutrophil count (ANC) <0.5×10^9^/L or platelet count (PLT) < 20×10^9^/L - Serum creatinine > 2.0 mg/dL or creatinine clearance < 40 mL/min measured or calculated by Cockroft-Gault equation. - Patients with poor compliance should not be included in the study based on the judgment of the research team, for example if they refused to take medicine at will many times during the previous treatment.   **Study Drug, Dosage, and Mode of Administration:**  **Ruxolitinib plus corticosteroids treatment (ruxolitinib group):**  The initial dose of methylprednisolone is 1 mg/kg/day intravenously given in this arm for at least 7 days. The dosage of ruxolitinib is 5 mg PO QD. CSA will be administered intravenously at a dose of 2 mg/kg twice daily, targeting minimum concentration levels of 150–250 ng/mL. If GVHD response to treatment is assessed as PR/CR at 7 days, methylprednisolone will be tapered, followed by reduction and discontinuation of CSA and then ruxolitinib. The reduction of the methylprednisolone in the ruxolitinib group is gradual, suggesting it be tapered off over 6 weeks as follows: dosage reduced to 0.6 mg/kg/day, 0.4 mg/kg/day, 0.3 mg/kg/day, 0.25 mg/kg/day, and 0.18 mg/kg every 5 days, followed by 0.1 mg/kg/day at week 4, 0.1 mg/kg every other day after 5 days and stopped at week 6. After steroid discontinuation and CR or stable PR maintained for 6 weeks, CSA is tapered over 60 days. After CSA discontinuation and no presence of recurrent GVHD, ruxolitinib is tapered off over 90 days, which is totally maintained for approximately 6 months.  **Corticosteroid treatment (corticosteroids group):**  The initial dose of methylprednisolone is 2 mg/kg/day given twice daily for at least 7 days and then reduced. The dosage of methylprednisolone in the corticosteroids group is decreased gradually after CR and tapered off over 10 weeks as the following: dosage reduced to 1 mg/kg/day to 0.6 mg/kg/day, 0.4 mg/kg/day, 0.3 mg/kg/day, 0.25 mg/kg/day, and 0.18 mg/kg every 7 days, and then 0.1 mg/kg/day at week 4, 0.1 mg/kg every other day after 5 days, and stopped at week 10. CsA was administered intravenously at a dose of 2 mg/kg twice daily, targeting minimum concentration levels of 150–250 ng/mL. The recommended duration of CsA is 6 months.  In both arms, for refractory acute GVHD, i.e., the progression of GVHD after 3 days of therapy, no improvement within 7 days, or no CR after 14 days of therapy, the second-line therapy will be started. For refractory acute GVHD or recurrent acute GVHD, basiliximab may be used as second-line therapy, and other alternative drugs included methotrexate or mesenchymal stem cells may be used at the researcher’s decision. For refractory acute GVHD, methylprednisolone is discontinued and CsA is continued in both arms. Prolonged maintenance of ruxolitinib is used in the ruxolitinib group. A standardized follow-up booklet is given to each enrolled patient for recording the dose, frequency, and administration method of the drugs. **Estimated Duration of Participation:** Subject participation is expected to average 24 months, which includes the following:   - A screening period lasting up to 28 days. - A treatment period lasting as long as the subject is benefiting from treatment. - A safety follow-up period lasting 180 days after treatment ends. - A survival follow-up period lasting until death or study withdrawal. \| \| \| **Estimated Number of Subjects:** 198 subjects. \| \| \| **Principal Coordinating Investigator:** [name] \| \| \| **Statistical Methods:**  The sample size is calculated according to the primary endpoint (ORR) of the study. Based on our published phase I study of 32 acute GVHD patients who received steroids as first-line therapy, an expected proportion of 55% for the patients treated with corticosteroids only was established. Based on our published data of patients with acute GVHD grade I–IV who received steroid-ruxolitinib (5 mg/day) as first-line therapy, the ORR was 82.05%. Patients with acute GVHD grade I were also included in the phase I analysis. Thus, an expected proportion of 75% for the patients treated with steroid-ruxolitinib (5mg/day) was established. This study is planned to detect a response difference between treatment arms at a two-sided significance level α=5% with a power of 1-β=80%. The sample size was estimated using PASS software based on the primary endpoint (ORR). Allowing a withdrawal rate of 10%, 198 patients (99/group) will be required.  Continuous data are described as median with interquartile range (IQR) or mean and standard deviation (SD) according to the normality of distribution. The categorical data are described as n (%). The ORR was calculated with its 95% confidence interval (CI) and compared by the stratified Cochran–Mantel–Haenszel test. Additionally, a logistic regression model, which included aGVHD risk (high vs. intermediate), and disease status before transplantation (CR vs. no CR) as covariates, was established to explore the association between treatment and ORR on day 28. Post-hoc subgroup analysis was performed by biomarker risk, age and GVHD grade, although these were not prespecified in the protocol. The cumulative incidence of recurrent aGVHD was analysed using the Fine and Gray test in a competing risk framework. The Kaplan–Meier method was used to estimate the ORR on day 56, OS, DFS, and FFS, and the log-rank test was used to evaluate the difference between the groups. The cumulative incidence rates of NRM and relapse were estimated using a competing risk model and compared using the Fine and Gray test. A Cox proportional hazard regression model was used for multivariable regression analysis for OS and DFS. Multivariable regression analysis was performed for NRM using the Fine–Gray proportional hazard regression for competing events. The following variables were included in the univariable analysis: primary disease, cytogenetic risk, age and gender of the donor and recipient, source of graft, treatment arm, aGVHD risk, and disease status before transplantation. Variables with P<0.1 in univariate analysis or variables known to influence the outcomes were included in the multivariable analysis. Competing events were defined as follows: for GVHD, death without the event; for relapse, death without relapse; and for NRM, relapse. Any difference for which the two-sided P<0.05 was considered statistically significant. All analyses were carried out using SPSS 22.0 software (IBM Corporation, Armonk, NY, USA) or R version 4.1.2 (www.cran.r-project.org). All statistical analyses were based on the intend to treat set. \| \| | |

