### 5.4.1. Withdrawal Criteria

Subjects must be withdrawn from study treatment for the following reasons:

- The subject has experienced an unacceptable toxicity.
- Relapse of underlying malignancy.
- The subject is unable to tolerate ruxolitinib at a dose of 5 mg QD.
- Additional systemic therapy is required for GVHD progression or lack of response, including corticosteroid doses greater than those used on Study Day 1.
- Further participation would be injurious to the subject's health or well-being, in the investigator's medical judgment.
- The subject becomes pregnant.
- Consent is withdrawn.
- The study is terminated by the sponsor.

A subject **may** be withdrawn from study treatment as follows:

- If, during the course of the study, a subject is found not to have met eligibility criteria, then the medical monitor, in collaboration with the investigator, will determine whether the subject should be withdrawn from the study.
- If a subject is noncompliant with study procedures or study drug administration in the investigator's opinion, the sponsor should be consulted for instruction on handling the subject.

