### 8.3.2. Secondary Analyses

The estimated rates with two-sided 95% confidence intervals (CIs) are used for secondary endpoints (proportion of CR patients and patients who stopped treatment). The ORR on day 28 is calculated with its 95% CI. Kaplan–Meier method is used to estimate the DOR, OS, and DFS, and the log-rank test is used to evaluate the difference between the groups ^[21]^. The cumulative incidence of NRM and relapse is estimated using a competing risk model and compared using the Fine and Gray test. The Cox proportional hazard regression model is used for multivariable regression analysis for OS and DFS. The multivariable regression analysis for NRM is performed using the Fine–Gray proportional hazard regression for competing events. Potential risk factors considered in the regression analysis include primary disease, cytogenetic risk, age and gender of the donor and recipient, graft source, treatment arm, acute GVHD risk, and disease status before transplantation. The cumulative incidence of recurrent acute GVHD is analyzed using the Fine and Gray test in a competing risk framework. The threshold for statistical significance is set at 0.05, and all tests are two-sided. All analyses are carried out using SPSS 22.0 software (IBM Corporation, Armonk, NY, USA) and R version 4.1.2 (www.cran.r-project.org). The treatment-induced differences in OS and DFS will be based on the Cox proportional hazard regression model. The reported treatment difference in NRM and relapse will be based on the multivariate analysis using Fine–Gray proportional hazard regression.

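### Two secondary durability analyses do not fit their endpoints: DOR censors deaths and discontinuations, and the Synopsis assigns Kaplan–Meier and log-rank to the Day-56 durable ORR, which is a proportion

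*Protocol*

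**What the plan says.** **DOR.** Section 2 and the Synopsis define it for responders, at Month 6: "The DOR is defined from the time of the onset of response to loss of response". The censoring rule follows: "Subjects who died or discontinued will be censored at the" "death date or the previous assessment". Section 8.3.2 gives the method: "Kaplan–Meier method is used to estimate the DOR, OS, and DFS, and the log-rank test is used to evaluate the difference between the groups".

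**Discontinuation.** Section 5.4.1 lists the reasons for which study treatment must be stopped. One is "Additional systemic therapy is required for GVHD progression or lack of response". Others are unacceptable toxicity, relapse of the malignancy, pregnancy and withdrawn consent.

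**Neighbouring rules.** The next endpoint in Section 2, response duration, counts added immunosuppressants for GVHD as an event and has no rule for death. The Synopsis names death without the event as the competing event for GVHD, and analyses recurrent acute GVHD by Fine and Gray.

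**Durable ORR at Day 56.** Section 2 and the Synopsis define it as follows: "defined as the proportion of patients in each arm whose response on day 28 lasts until day 56 after randomization". The statistical methods in the Synopsis say: "The Kaplan–Meier method was used to estimate the ORR on day 56, OS, DFS, and FFS", with the log-rank test for the comparison. Section 8.3.2 does not list this endpoint under Kaplan–Meier. The Synopsis bases all analyses on the intention-to-treat set, and Section 8.4 includes all randomised participants for all outcomes.

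**The concern.** Kaplan–Meier treats a censored patient as having the same future as those still under observation. A responder who dies cannot later lose the response, and a responder withdrawn because GVHD needs more treatment is not like one who remains in response. Censoring both gives a curve that sits above the proportion alive and in response. The excess is larger in whichever arm has more deaths or failure-driven discontinuations among its responders, so the comparison between arms can be distorted as well as the level.

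The rule also conflicts with its neighbours. The same patient, given an added immunosuppressant, is an event under response duration and may be censored under DOR. The term discontinued may not mean the same in the two arms. Section 5.1.1.1 allows ruxolitinib to be maintained in refractory GVHD, the Synopsis stops methylprednisolone in both arms in that setting, and Section 5.4.1 requires withdrawal when systemic therapy is added. These passages must be reconciled before the word can carry a censoring rule.

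For Day 56, a method for event times is attached to an outcome that is either present or absent on a fixed day. What the analysis estimates then depends on choices that the protocol does not state.

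**Working it through.** **The plan's own figure.** The documents give no figure for either durability endpoint. The only design figure to reproduce is the sample size for Day-28 ORR. With 55% vs 75%, two-sided 5%, 80% power and pooled variance under the null:

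n = [1.96·√(2·0.65·0.35) + 0.8416·√(0.55·0.45 + 0.75·0.25)]² / 0.20² = 88.1, so 89 per arm; 89/0.90 = 98.9, so 99 per arm and 198 in total.

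It reproduces, and nothing below changes it.

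**DOR, deaths censored.** Assume constant monthly hazards in responders: l for loss of response and m for death in response. At Month 6, Kaplan–Meier with deaths censored estimates exp(−6l). The proportion alive and in response is exp(−6(l+m)).

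The documents give neither hazard. I assume l = 0.05. For m, the only anchor is the phase I 1-year overall survival of 73.4% (Section 1.3). It implies −ln(0.734)/12 = 0.026 per month for deaths of every kind. Half of that, 0.013, is taken as the low value and 0.03 as the high value.

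| m | Kaplan–Meier | Alive and in response | Gap |
|---|---|---|---|
| 0.013 | exp(−0.300) = 74.1% | exp(−0.378) = 68.5% | 5.6 points |
| 0.03 | exp(−0.300) = 74.1% | exp(−0.480) = 61.9% | 12.2 points |

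The cumulative incidence of loss, with death as a competing risk, is l/(l+m)·[1 − exp(−6(l+m))]: 25.0% and 23.8%, against 1 − 74.1% = 25.9% from Kaplan–Meier. So the curve overstates the chance of being alive and in response, and slightly overstates the incidence of loss. It estimates neither.

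**DOR, arms with different mortality.** Take a 31.2% loss in both arms (the phase I recurrence figure in Section 1.3, borrowed as an assumption) and assumed death in response of 5% vs 20%, independent of loss. Kaplan–Meier reads 1 − 0.312 = 68.8% in both arms. Alive and in response are 0.688·0.95 = 65.4% and 0.688·0.80 = 55.0%.

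**DOR, losses recorded as discontinuations.** Take a cumulative incidence of 31.2% for loss and an assumed 10% for death. Then 1 − 0.312 − 0.10 = 58.8% are alive and in response. The cumulative loss hazard is −ln(0.588)·0.312/0.412 = 0.402, and Kaplan–Meier reads exp(−0.402) = 66.9%. If a quarter or a half of the losses were coded as censored discontinuations, it would read exp(−0.302) = 74.0% or exp(−0.201) = 81.8%. The share is not known; these values only show the direction.

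**Day 56.** Use the planned Day-28 ORR of 75% vs 55%, and assume that 80% of responders hold to Day 56 in both arms. The defined endpoint is 0.75·0.80 = 60% vs 0.55·0.80 = 44%.

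- Curve in Day-28 responders only: 80% vs 80%. The planned difference disappears.
- Curve in all randomised patients, non-responders failing at Day 28, no censoring: 60% vs 44%. The estimate is right, but log-rank tests the pattern of event times rather than the difference in these proportions. Any censored patient is also treated as still able to hold the response, not as not durable.

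**The case against.** Several objections carry weight.

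- **Which failures are censored.** A reader might infer that the rule censors the failures themselves. The text does not support that. The DOR event is loss of response, so death is a competing event; withdrawal for toxicity, relapse, pregnancy or consent is not a loss of GVHD response. For a patient withdrawn for GVHD progression, the progression might be recorded as the event first, since Section 2 sets no precedence. What stands is that the rule as written can remove losses, and that this censoring is tied to outcome.
- **Size.** A reader might take a wider gap, for example 74% vs 55% with 5% monthly death in response. That hazard implies 1 − exp(−0.60) = 45% dead at one year, against 26.6% in phase I. The upper value of 3% used above already exceeds the phase I rate for all deaths, although phase I also included grade I disease.
- **Day-56 population.** A reader might infer that the plan would report 80% where the endpoint is 44%. That needs a responder-only curve, which no section specifies; the Synopsis and Section 8.4 point to all randomised patients. The method also appears only in the Synopsis. The mismatch between definition and test remains.
- **Other endpoints.** Failure-free survival counts progression, relapse, non-relapse death and new acute GVHD therapy from randomisation, and recurrent acute GVHD is analysed with competing risks. Durability will not rest on DOR alone. This limits the harm but does not correct DOR.
- **The DOR log-rank test.** DOR is openly restricted to responders. Comparing arms within that subset is not a randomised comparison, but dropping the test is a preference. Labelling it suffices.

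A statistical analysis plan might settle some coding. The censoring rule and the Day-56 method are, however, positive statements in the protocol, not omissions.

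**Conclusion.** The point holds for two secondary analyses. As written, the DOR rule censors informatively, departs from the protocol's own treatment of death for GVHD, and contradicts the response duration endpoint on added immunosuppression. Under assumed constant hazards of 5% per month for loss and 1.3% to 3% for death in response, Kaplan–Meier exceeds the proportion alive and in response at Month 6 by about 6 to 12 points. The documents give no rate of death in response, so this range is an illustration and not an estimate. Any further effect of coding losses as discontinuations cannot be sized.

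For durable ORR at Day 56, the Synopsis method does not match the definition, and Section 8.3.2 does not repeat it. How far the result would be off depends on the population used, which ranges from no error in the estimate to loss of the whole planned difference.

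A reader might infer that the main efficacy conclusion is at risk. It is not: the Day-28 ORR and its sample size do not depend on either rule.

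**What to change.** **DOR.** Count loss of response and start of new systemic GVHD therapy as events. Treat death in response either as an event or as a competing risk reported by cumulative incidence. Do not censor at treatment discontinuation while GVHD follow-up continues. Define discontinued, state whether event or censoring takes precedence, and align DOR with response duration, or say plainly how they differ. Describe any between-arm DOR comparison as conditional on having responded.

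**Durable ORR at Day 56.** Analyse it as a binary proportion of all randomised patients with the stratified Cochran–Mantel–Haenszel test that the Synopsis names for ORR. Count Day-28 non-response, and death, new GVHD therapy or a missing assessment by Day 56, as not durable. Make the Synopsis and Section 8.3.2 agree.

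**Cost.** Analysis wording only, made before results are seen. Sections 6.5.2, 6.5.3 and 7.5.1 already provide for GVHD grading, new-therapy and survival data after treatment ends. One check is needed: Section 7.5.1 schedules grading every 28 days after week 8, but for patients who stopped for reasons other than GVHD progression it also points to the safety follow-up visit, which Section 6.5.1 places 180 days after the end-of-treatment visit. With death and new therapy counted as events, the DOR figures will look less favourable.
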